**Figure 2. F2:**
[figure not shown]
Example of fluorescence of lymph node groups recorded during surgical procedure (sigmoid resection case). Fluorescence of paracolic nodes (a.) and along vascular tie (b.) is recorded and depicted to ensure proper lymphatic node group and ICG spread marking after specimen removal.

**Figure 3. F3:**
[figure not shown]
Example of specimen marking (sigmoid resection). Tags are attached to the specimen according to Japanese classification of lymphatic node groups^[15]^. Segments of D1 collector are named according to Japanese Classification of pericolic lymphatic collector groups^[16]^. IO and IA marks are borders of D1 ICG spread visualized during surgical procedure. So, the area of ICG fluorescence is projected on lymphatic node groups harvested during surgery.

**Table 2 T2:** Protocol synopsis

Title	ICG fluorescence guided lymph node mapping for determination of bowel resection margins in colon cancer
Study design	Patients with primary resectable colon cancer are assigned for colonic resection with intraoperative ICG lymphatic mapping. The dye’s mesenteric distribution is marked by surgeon on the specimen. During pathological examination each lymph node is assessed both for presence of metastases and for its exact location in relation to primary tumor and margins of indocyanine distribution.
Aims and endpoints	*Aim of the study:*
	To determine if ICG lymphatic mapping sensitivity is sufficient to guide resection margins selection in colon cancer surgery by comparing lymphatic distribution of subserosally injected dye to the actual spread of lymphatic metastases reported by pathologists after specimen examination.
	*Primary endpoint:*
	Proportion of pN+ patients with affected lymph nodes detected only within margins of ICG distribution.
	*Secondary endpoints:*
	incidence of adverse events related to ICG lymphatic mapping; feasibility of ICG lymphatic mapping for colon cancer (proportion of ICG spillage affecting interpretation); incidence of lymph node metastases outside conventional resection margins (10 cm); colon cancer lymphatic spread patterns; proportion of operations which extent is effected by ICG lymphatic mapping.
Patients	Female and male patients 18 years or older with signed informed consent and diagnosed primary colon cancer T1-4aN0-2bM0-1b
Number of patients	101
Study duration	The study is conducted starting from 26 July 2022, until target number of patients is enrolled
Estimated time until target number of patients is reached	2 years
Statistical analysis	If after 101 ICG lymphatic mapping procedures we record sensitivity of 96% or higher, it will mean that this method might be considered as a reliable tool to visualize locoregional lymphatics of a colon segment affected by a tumor.

There is no blinding of investigators or patients in current study.

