#### Endpoints

Primary endpoint
Proportion of pN+ patients in which affected lymph nodes are detected only within margins of ICG distribution (number of patients with affected lymph nodes located within ICG distribution margins divided by the number of all patients with pN+).

Secondary endpoints
Incidence of adverse events related to ICG lymphatic mapping (time frame: 30 days after operation);feasibility of ICG lymphatic mapping for colon cancer (proportion of cases with ICG spillage affecting interpretation);incidence of lymph node metastases outside conventional resection margins – 10 cm (proportion of patients with aberrant lymphatics leading to affected lymph nodes);colon cancer lymphatic spread pattern (descriptive data on incidence of D1, D2 and D3 lymphatic collector metastases and frequencies of D1 collector metastases depending on distance from primary tumor);proportion of operations which extent is effected by ICG lymphatic mapping (number of patients with change of operation plan due to mapping results divided by the number of patients).

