#### Morphological assessment

Groups of lymph nodes and margins of indocyanine lymphatic spread are marked on non-fixed specimen by a member of a surgical team taking part in the procedure and determined by surgeon in charge of clinical case. Lymph nodes are marked according to Japanese classification^[15]^ depending on performed extent of colonic resection and lymphadenectomy (Fig. 3).

Specimen assessment is performed according to principles, described by N. West *et al*^[17,18]^, protocol of pathology assessment is described in Appendix S2 http://links.lww.com/ISJP/A8 section.

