#### Pathology report

Pathological examination includes macroscopic and microscopic assessments, described in Appendix S2 http://links.lww.com/ISJP/A8 section. During pathological examination each lymph node is assessed both for presence of metastases and for its exact location in relation to primary tumor and margins of indocyanine distribution.

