### Sample size calculation and statistical analysis

As the study is aimed to access if ICG mapping can be used to reliably define resection margins in colon cancer surgery, a case of affected lymph nodes only within fluorescence margins was regarded as a true positive case, no fluorescence in pN0 – true negative, pN+ because of metastatic lymph nodes outside fluorescence zone – false negative, pN0 despite presence of fluorescence – false positive.

Sample size of 101 patients was calculated using Buderer method^[19]^ with a confidence level (1 – *α*) of 0.95 as a minimum of cases required to test accuracy of lCG lymphatic mapping for estimated sensitivity of 0.99 and precision (margin of error) of 0.03. This resulted in sensitivity threshold of 0.96. The calculation was performed for minimum acceptable kappa (k0) of 0.6, expected kappa (k1) 0.9. The resultant estimated power (1 – *β*) is 0.96. The average of pN+ cases in our center (42%) was used as prevalence – proportion of outcome (p).

For statistical analysis of primary endpoint, sensitivity will be calculated according to standard formula (number of true positive cases divided by sum of true positive and false negative cases) and its meaning will be compared to the estimated 0.99 ± 0.03. For analytical purposes other measures of accuracy will be calculated as well.

“Intent-to-treat” analysis will be performed, thus once enrolled patients are to be analyzed, irrespective of received treatment. To focus on specificities ICG spread regardless of influence of patients with treatment deviations and those with unsuccessful ICG injection, “per-protocol” analysis will be performed as well.

For secondary endpoints type of analysis will depend on nature of the data. Descriptive statistics will be used to depict feasibility of ICG lymphatic mapping, incidence of adverse events, incidence of lymph node metastases outside conventional resection margins and proportion of operations which extent is affected by ICG lymphatic mapping. Lymph node metastases pattern will be assessed as calculation of frequency of affected nodes related to number of studied nodes in each group. Parametric and non-parametric criteria will be used to compare mean values and contingency tables.

In cases of missing data, should more than 10% of data be missing, the variable will be deleted, because estimates are likely to be biased^[20]^. In other situations multiple imputations will be used.

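### Node search, and the placement of nodes near the border, are done with the ICG border tagged on the specimen and no masking described: a risk of bias in the primary sensitivity

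*Protocol article*

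**What the plan says.** The blinding statement, after Table 2 in the Trial design section of the protocol article, reads: "There is no blinding of investigators or patients in current study". It makes no exception for pathology, and none appears elsewhere in the article.

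The border is put on the specimen before pathology receives it. Under Morphological assessment: "Groups of lymph nodes and margins of indocyanine lymphatic spread are marked on non-fixed specimen by a member of a surgical team". The Figure 3 legend explains the tags: "IO and IA marks are borders of D1 ICG spread visualized during surgical procedure".

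The Pathology report section then sets the task: "each lymph node is assessed both for presence of metastases and for its exact location in relation to primary tumor and margins of indocyanine distribution". The Design section describes the same task and adds that every node is assigned to a Japanese node group, and D1 nodes also to a distance from the tumour.

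The primary endpoint (Endpoints section) is the "number of patients with affected lymph nodes located within ICG distribution margins divided by the number of all patients with pN"+. In the sample size section, a false negative is a pN+ case "because of metastatic lymph nodes outside fluorescence zone".

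Details of the pathology work are referred to Appendix S2, which is not at hand.

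**The concern.** The trial compares an index test (the ICG map) with a reference standard (which nodes are metastatic and where they lie). A false negative enters the data only if a metastatic node is retrieved, read as positive and placed outside the tagged border. Two of these steps leave room for judgement: how thoroughly tissue beyond the border is searched, and to which side a node at the border is assigned. As described, both are carried out with the border visible.

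If those judgements lean towards the map, false negatives disappear and the observed sensitivity rises. The consequence is practical. Under Objectives and study hypothesis, the absence of affected nodes beyond the ICG spread, in patients whose fluorescent zone is smaller than the conventional margins, is to count as grounds for a smaller resection. A missed false negative bears directly on that inference.

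A single-arm surgical design explains why the surgeon cannot be masked. It does not explain leaving pathology unmasked, and the article gives no reason for it.

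**Working it through.** **Inputs from the protocol article** (Sample size calculation and statistical analysis): "estimated sensitivity of 0.99 and precision (margin of error) of 0.03"; confidence level 0.95, so z = 1.96; pN+ prevalence 42%; sensitivity threshold 0.96.

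**1. The plan's own figure.** Buderer method:
- pN+ patients needed = z² × Se × (1 − Se) / d² = 1.96² × 0.99 × 0.01 / 0.03² = 42.26
- total = 42.26 / 0.42 = 100.6, rounded up to 101

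The stated 101 is reproduced. The expected number of pN+ patients is 101 × 0.42 = 42.4, about 42.

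**2. The pass rule at 42 pN+ patients.** A patient with any affected node outside the border is counted as a false negative, since the endpoint requires affected nodes only within it.

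| False negatives | Sensitivity | Against 0.96 |
|---|---|---|
| 0 | 42/42 = 1.000 | pass |
| 1 | 41/42 = 0.976 | pass |
| 2 | 40/42 = 0.952 | fail |

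The abstract asks for more than 96% and Table 2 for 96% or higher; at this number of patients the two give the same verdicts. At 43 pN+ patients the pattern is unchanged (42/43 = 0.977, 41/43 = 0.953).

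**3. Losing one of two false negatives.**
- The outside node is placed inside, or is missed in a patient who also has affected nodes inside: 41/42 = 0.976, pass.
- The patient's only affected node is missed, so the patient becomes pN0 and leaves the denominator: 40/41 = 0.976, pass.

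The sensitivity is the same to three decimals by either route, and the verdict reverses.

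**4. Illustration of scale.** The true false-negative rates q and the lost fractions L are assumptions; the documents give neither. L is the share of false-negative patients recorded as true positives, so the apparent rate is p = q × (1 − L). The chance of passing is P(X ≤ 1) = (1 − p)^42 + 42 × p × (1 − p)^41.

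| True rate q | L = 0 | L = 25% | L = 50% |
|---|---|---|---|
| 5% | 0.372 | 0.529 | 0.717 |
| 7% | 0.197 | 0.345 | 0.565 |
| 10% | 0.068 | 0.167 | 0.372 |

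For example, with q = 7% and L = 25%, p = 0.07 × 0.75 = 0.0525 and the chance is 0.345.

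**5. What existing checks cover.** The Quality control section provides recordings of surgery and photographs of the marked fresh specimen. The Data quality section provides verification of entered data and comparison of surgical details with the recordings. These cover the marking and the data entry, and can support a later check of placement. None covers how thoroughly nodes were searched for.

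**The case against.** **Who does what is not stated.** A reader might infer that one pathologist retrieves, reads and places every node. The article does not say so: the pathology sections are in the passive, and Table 2 speaks of pathologists in the plural. The point needs only that these tasks belong to one pathology examination of a tagged specimen.

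**The blinding statement does not name pathologists, and Appendix S2 is not shown.** It would go too far to say that the article rules out masking them. The appendix may specify retrieval, order of reading or masking. This stands, and it lowers confidence. Even so, the article itself sets out visible border tags, a pathology task defined against them, and an unqualified statement on blinding. If the appendix masks pathology, that statement needs the exception.

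**Placement can be re-checked.** A reader might conclude that no later analysis could repair the damage. That is too strong. Node group, D1 distance, specimen photographs and recordings allow borderline placement to be reviewed. Only a node never retrieved is beyond correction.

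**Discretion is limited.** The surgical team fixes the border before pathology, the IO and IA tags are described for D1 only, and there is no evident way for a tag to change a microscopic reading. A patient-level false negative is lost only if every affected outside node in that patient is missed or misplaced. All of this stands and narrows the point to search and borderline placement.

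**The direction could be the opposite.** A pathologist who sees the border might search harder beyond it, since outside metastases are what the trial looks for. A borderline node wrongly placed outside would turn 41/42 into 40/42. This also stands. The one-patient margin comes from the threshold and the number of pN+ patients; it shows how sensitive the verdict is and does not measure the bias.

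**Conclusion.** The point holds as a risk of bias. On what the article states, node search and the placement of nodes near the border take place with the index test visible, and no masking is described. A reader might go further and infer that the reported sensitivity will be too high; the documents do not support that, because they give no information on the direction or size of any effect.

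Inflation deserves attention because at about 42 pN+ patients one lost false negative turns a fail (0.952) into a pass (0.976), and a pass may be used to argue for smaller resections. The illustrative chances of passing rest wholly on assumed false-negative rates and loss fractions. The conclusion also assumes that Appendix S2 contains no masking. The change is worth making because it needs no additional reader or procedure and leaves the sample size at 101.

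**What to change.** **For specimens from now on:**
- Replace the IO and IA tags with neutral coded tags of one kind, placed at the ICG borders and also at standard stations and distances.
- Have pathology retrieve, read and report nodes by station, tag interval and distance from the tumour, without access to the operative ICG findings.
- Let someone outside pathology, such as the research physician, hold the key, and derive inside or outside status only after the pathology report is signed.
- Amend the blinding statement to the effect that patients and surgeons are not masked and that pathologists are masked to the ICG margins. If Appendix S2 already provides this, say so there and cite it.

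**For patients already processed** (enrolment began on 26 July 2022): re-derive placement from the recorded station, distance and specimen photographs, and report the primary result separately before and after the change. This cannot recover nodes that were never retrieved.

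**Cost:** some extra bookkeeping per specimen, one linking step in the database, and two tagging procedures within the 101 patients. A node lying exactly at a coded tag still needs a judgement, but one made without knowing whether that tag is the ICG border. Patient treatment is not affected.

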#### Endpoints

Primary endpoint
Proportion of pN+ patients in which affected lymph nodes are detected only within margins of ICG distribution (number of patients with affected lymph nodes located within ICG distribution margins divided by the number of all patients with pN+).

Secondary endpoints
Incidence of adverse events related to ICG lymphatic mapping (time frame: 30 days after operation);feasibility of ICG lymphatic mapping for colon cancer (proportion of cases with ICG spillage affecting interpretation);incidence of lymph node metastases outside conventional resection margins – 10 cm (proportion of patients with aberrant lymphatics leading to affected lymph nodes);colon cancer lymphatic spread pattern (descriptive data on incidence of D1, D2 and D3 lymphatic collector metastases and frequencies of D1 collector metastases depending on distance from primary tumor);proportion of operations which extent is effected by ICG lymphatic mapping (number of patients with change of operation plan due to mapping results divided by the number of patients).

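### Two operative phrases of the primary endpoint do not match its evident intent that a pN+ patient with metastatic nodes both inside and outside the ICG zone is a failure

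*Protocol article*

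**What the plan says.** The Endpoints section of the protocol article states the primary endpoint twice in one item.

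- **In words:** the proportion of pN+ patients whose "affected lymph nodes are detected only within margins of ICG distribution".
- **In brackets, as numerator and denominator:** the "number of patients with affected lymph nodes located within ICG distribution margins divided by the number of all patients with pN" (that is, pN+).

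The worded form, with *only*, also stands in the Abstract (Methods), Table 1 and Table 2. The bracketed form is the only explicit fraction given for the endpoint.

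The section Sample size calculation and statistical analysis then sets up a two-by-two classification. A true positive has affected nodes only inside the fluorescence margins. The false-negative cell is "pN+ because of metastatic lymph nodes outside fluorescence zone – false negative". Sensitivity is the "number of true positive cases divided by sum of true positive and false negative cases".

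The scenarios under Objectives and study hypothesis place affected nodes either within or outside the fluorescence zone and name no mixed category. Nowhere does the article expressly assign a patient who has both.

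**The concern.** Take a patient with one positive pericolic node inside the ICG zone and another positive node beyond it. The worded endpoint makes this patient a failure. The bracketed formula, followed as written, makes the patient a success, because there are affected nodes within the margins. Under the analysis section the patient is not a true positive. The patient is a false negative only if any outside node is enough; if pN+ status must be *because of* the outside nodes, a patient already pN+ from inside nodes fits neither cell and leaves TP + FN.

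This matters because the trial asks whether resection can be reduced to fit the ICG spread. In a mixed patient that reduction would leave metastatic nodes behind, so a rule that counts the patient as a success, or omits the patient, works against the aim. The decision also rests on few patients, so the classification of one or two can settle it.

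**Working it through.** **Inputs, all from Sample size calculation and statistical analysis unless noted**

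- Confidence level 0.95, taken as two-sided (z = 1.96). Sidedness is not stated but is implied by a margin of error.
- "estimated sensitivity of 0.99 and precision (margin of error) of 0.03".
- Prevalence: "The average of pN+ cases in our center (42%) was used as prevalence".
- Success rule: observed sensitivity of 96% or higher (Table 2). The Abstract says above 96%; the difference does not matter at 42 pN+ patients.

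**Step 1. The plan's own figure**

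TP + FN = z² × Se × (1 − Se) / d² = 1.96² × 0.99 × 0.01 / 0.03² = 42.26.

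N = 42.26 / 0.42 = 100.6, rounded up to 101. The stated figure reproduces. The expected number of pN+ patients is 101 × 0.42 = 42.4, taken as 42 below.

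Dividing TP + FN by the pN+ prevalence is valid only if TP + FN is the whole pN+ group. The calculation therefore assumes that no pN+ patient drops out of the table.

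**Step 2. Failures allowed**

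At 42 pN+ patients, 41/42 = 97.6% meets the rule and 40/42 = 95.2% does not, so one failure is allowed. Under the rule in Table 2 the allowance is one for any pN+ count from 25 to 49, and two at 50 or 51.

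**Step 3. The same 42 patients under each reading**

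| Outside-only | Mixed | Mixed = failure | Mixed = success | Mixed dropped |
|---|---|---|---|---|
| 0 | 1 | 41/42 = 97.6%, met | 42/42 = 100%, met | 41/41 = 100%, met |
| 0 | 2 | 40/42 = 95.2%, not met | 42/42 = 100%, met | 40/40 = 100%, met |
| 1 | 1 | 40/42 = 95.2%, not met | 41/42 = 97.6%, met | 40/41 = 97.6%, met |

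One mixed patient alone does not change the verdict. Two mixed patients do, and so does one mixed plus one outside-only patient. In these cases the success and dropped readings agree, so the split that matters is failure against the other two.

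**Step 4. How often the verdict would differ**

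The documents give no rate of mixed patients, so the rates q below are assumptions. With 42 pN+ patients and no outside-only patients, the failure and success readings disagree when at least two patients are mixed: 1 − (1 − q)^42 − 42q(1 − q)^41. If 1% of pN+ patients are outside-only, disagreement requires at most one outside-only patient and at least two failures in total.

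| Assumed mixed rate | No outside-only | 1% outside-only |
|---|---|---|
| 1% | 0.07 | 0.14 |
| 2% | 0.21 | 0.29 |
| 3% | 0.36 | 0.44 |
| 5% | 0.63 | 0.66 |
| 10% | 0.93 | 0.89 |

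**The case against.** The strongest reply is that the article has one intended reading and two loose phrases. *Only within* appears in every worded statement of the endpoint and in the true-positive definition. The brackets gloss a phrase that already says *only*. Objectives and study hypothesis says that metastases beyond the ICG margins count against sensitivity, with no exemption for patients who also have nodes inside. The dropped reading conflicts with the all-pN+ denominator in Endpoints and with the sample size step, and it needs *because of* to mean *solely because of*. This stands: the intent is failure.

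It follows that a reader should not infer three equally live readings. Nor do the documents support the inference that mixed patients will be the main kind of failure; that needs an assumption about stepwise spread for which no rate is given. The design assumes a total failure rate of 1% (sensitivity 0.99). If every failure at that rate were mixed, the verdict would differ with probability 0.07; the larger probabilities require rates above the design value.

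It can also be said that a fuller protocol or SAP may hold the rule. That would excuse silence, but here the article's only explicit fraction conflicts with the words it is meant to express. Clear intent makes the correction easy; it does not make the formula right.

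**Conclusion.** The point holds as a mismatch between intent and operative wording. The bracketed formula literally counts a mixed patient as a success, and the false-negative definition does not clearly count that patient as a failure. The consequence is conditional: with about 42 pN+ patients and the 96% rule, it takes two mixed patients, or one mixed plus one outside-only, to reverse the conclusion.

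A reader might go further and infer that reported sensitivity will be biased upward. The documents do not support that, because it presumes that the analyst adopts a reading which most of the text disfavours. What they do support is that the primary verdict has a margin of one patient, and that the patient type most in need of a rule has none written down. The illustration rests on 42 pN+ patients and on assumed mixed rates.

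**What to change.** 1. In Endpoints, insert *only* into the bracketed numerator, so that it counts pN+ patients whose affected nodes all lie inside the ICG margins.
2. In Sample size calculation and statistical analysis, define a false negative as any pN+ patient with at least one metastatic node outside the fluorescence zone, whether or not nodes inside it are also affected.
3. State that TP + FN equals all pN+ patients in the analysis set. This follows from the first two changes and is what the Endpoints denominator and the sample size calculation already assume.

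The cost is a few sentences. The sample size stays at 101, and no new data are needed, because Trial design and Pathology report already have each node located relative to the ICG margins. The only price is that reported sensitivity may be lower than under the loose readings.

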## Introduction

### Background and rational

Navigational surgery including mapping and tailoring of resection margins can be a solution to the major problem of colon cancer surgery: finding “the least possible not to compromise oncological safety” resection clearance for each patient. Mentioned concept has already been discussed^[1,2]^. But although the idea that all patients are different and therefore require different approaches sounds reasonable, this notion has not met sufficient response because yet there is no tool with proven effectiveness to implement it.

However, there is a lot of evidence on ICG fluorescent imaging for visualization of locoregional lymphatic paths of colonic lesions^[2,3]^, which can guide tailoring. ICG was firstly implemented as a sentinel lymph node detection (SLND) tool but was found to lack accuracy and standardization. Ankersmit *et al* analyzed 8 studies describing 227 SLN procedures in a meta-analysis in 2019 and observed low pooled sensitivity of 63%, negative predictive value 81% and detection rate of 94%^[4]^. The same year Villegas-Tovar *et al* reported similar findings in another meta-analysis of ICG SLND accuracy for colon cancer: they calculated detection rate of 91% (80–98%), sensitivity of 64.3% (51–76%), and specificity of 65% (36–85%) – and concluded that overall ICG performance for detection of lymph node metastases is poor^[5]^. So, it was shown that ICG does help to visualize lymphatics, but it does not work for SLND in colon cancer.

Moreover, assessment of fluorescence and fluorescent lymph node harvest are affected by multiple factors. In particular, 2023 systematic review and meta-analysis of 58 prospective designed studies by Lucas *et al* showed that injection time had a significant impact on aberrant drainage detection favoring preoperative tracer injection^[6]^. The same year Kinoshita *et al* in their series of 56 cases observed both cases with metastatic lymph nodes only in the area along the ICG-stained vascular pedicles and lymph node metastasis in areas along the ICG-unstained vascular pedicles^[7]^.

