#### Secondary aims of the study

To determine safety and feasibility of ICG lymphatic mapping, incidence of lymph node metastases outside conventional resection margins (10 cm), colon cancer lymphatic spread patterns and proportion of operations which extent is affected by ICG lymphatic mapping.

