### Trial design

#### Design

This is an interventional phase II trial with single group assignment investigating feasibility of defining colon resection margins for colon cancer with ICG by comparing lymphatic distribution of subserosally injected dye with actual spread of lymphatic metastases reported by pathologists after specimen examination.

This is a single center trial. To ensure adherence to the protocol and to avoid logistical and monitoring issues stemming from multicenter design, all patients are enrolled in one center. The study includes ICG lymphatic mapping procedure and extensive pathological evaluation of the specimen, which are not routinely performed in majority of centers. Also, the calculated sample size of 101 is a number of patients, which is possible to enroll in a single center during reasonable time period. So, the risks of type II error, methodological error leading to bias and contradicting results issue, resulting from single center approach were acknowledged and study protocol created to possibly minimize them and ensure that the statistical hypothesis is tested.

Since the main focus of the study is investigation of ICG lymphatic mapping feasibility and currently there is no gold standard of lymphatic mapping for colon, no control group was included.

After signing an informed consent and undergoing screening procedure eligible patients are assigned for colonic resection with ICG lymphatic mapping. The fluorescence is assessed before specimen removal (Fig. 2) and its mesenteric distribution is marked by surgeon on the specimen (Fig. 3). During pathological examination each lymph node is assessed both for presence of metastases and for its exact location in relation to margins of ICG distribution (each lymphatic node is classified according to Japanese classification of lymphatic node groups^[15]^; D1 nodes are also classified according to their distance from primary tumor^[16]^). All screening, intraoperative, postoperative, and pathological data is recorded for further analysis. Protocol synopsis is presented in Table 2.

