#### Surgical procedure

Surgical operation is performed under general anesthesia with or without thoracic epidural block. Lymphatic mapping procedure and fluorescence assessment are described in Appendix S1 http://links.lww.com/ISJP/A7 section. Date of surgery, data on operating surgeon and surgeon performing ICG mapping, and technical defects of ICG injection, including spillage, are recorded. Presence and time until pericolic fluorescence, fluorescence along feeding vessels, and aberrant fluorescence (if any is present), influence of ICG spread on resection margins, and intraoperative complications are traced and recorded in case report forms as well.

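### The feasibility endpoint counts only interpretation-affecting spillage, so patients with no fluorescence or another failed injection are left out of the failure proportion

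*Protocol article*

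**What the plan says.** Feasibility is a stated secondary aim (Secondary aims of the study: "To determine safety and feasibility of ICG lymphatic mapping"). The definition appears twice and both versions agree. Under Endpoints it is the "proportion of cases with ICG spillage affecting interpretation". The synopsis (Table 2) has "feasibility of ICG lymphatic mapping for colon cancer (proportion of ICG spillage affecting interpretation". No other failure mode is named in either place, and no threshold is set; the statistical section says only that feasibility will be described.

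Elsewhere the protocol acknowledges further ways in which mapping can fail:

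- Surgical procedure: "technical defects of ICG injection, including spillage, are recorded", which makes spillage one defect among others.
- Surgical procedure: "Presence and time until pericolic fluorescence, fluorescence along feeding vessels" and aberrant fluorescence go onto the case report form, so absence of fluorescence is a recordable outcome.
- Sample size calculation and statistical analysis: patients with an unsuccessful injection are a reason for the per-protocol analysis, and absent fluorescence in a pN0 patient is classed as a true negative.

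**The concern.** The trial asks whether the ICG border can guide resection margins. The first requirement is that a border can be seen and read. A patient with no fluorescence and no spillage has no such border, yet does not enter the failure proportion. The same holds for an injection that fails in some way other than spillage.

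This is not a detail that an article leaves to a fuller document. The operational definition is given, twice, and it is too narrow for the aim it serves.

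At stake is the descriptive answer on feasibility. None of the listed endpoints reports how often an attempted mapping gives an interpretable map. That share is also needed to read the per-protocol sensitivity, which is meant to set aside unsuccessful injections and is therefore conditional on the mapping having worked.

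**Working it through.** **The plan's own figure.** The feasibility endpoint has no stated figure. The sample size does, and it gives the denominator used below. Inputs from the statistical section: sensitivity 0.99, precision 0.03, confidence level 0.95, pN+ prevalence 0.42.

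- pN+ patients needed: 1.96² × 0.99 × 0.01 / 0.03² = 42.26
- Total: 42.26 / 0.42 = 100.6, rounded up to 101. The stated 101 is reproduced.

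**Which failures enter the numerator.** Setting the sections side by side:

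| Event | Foreseen or recorded | In the feasibility numerator |
|---|---|---|
| Spillage affecting interpretation | Yes (Surgical procedure) | Yes |
| Other technical defect of injection | Yes (Surgical procedure; per-protocol rule) | No |
| No fluorescence | Yes (Surgical procedure; accuracy table) | No |

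**Possible size.** The protocol gives no rate of absent fluorescence for this technique. The nearest figures are the ICG detection rates in the background section: 94% from one meta-analysis and 91% (80–98%) from another. Both concern sentinel-node detection. Two assumptions follow: that these rates carry over to mapping of the whole collector, and that non-visualised cases do not overlap with spillage cases. Expected patients without visualisation = 101 × (1 − detection rate):

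- 98%: 101 × 0.02 = 2.0
- 94%: 101 × 0.06 = 6.1
- 91%: 101 × 0.09 = 9.1
- 80%: 101 × 0.20 = 20.2

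**Effect on the reported figure.** Take the case of no interpretation-affecting spillage, with Clopper-Pearson 95% intervals:

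- As now defined: 0/101 failures, 0 to 3.6%
- Counting absent fluorescence at 94% detection: 6/101, 2.2 to 12.5%
- At 91% detection: 9/101, 4.2 to 16.2%

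**How much of this the primary endpoint would show.** Sensitivity uses pN+ patients only. If visualisation is independent of nodal status, the pN+ share of the missed cases is 0.42 × 6.06 = 2.5 to 0.42 × 9.09 = 3.8. The remaining 3.5 to 5.3 (6.06 − 2.55 and 9.09 − 3.82) are pN0 and do not enter sensitivity at all. The background cites a report of a negative correlation between pN+ and fluorescence, so the true split may lean more towards pN+.

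**The case against.** The strongest reply is that absent fluorescence is not ignored by the plan as a whole. A pN+ patient without fluorescence has affected nodes outside any fluorescent zone and would plausibly be a false negative in the intent-to-treat analysis, so the failure would count against the primary endpoint. A pN0 patient without fluorescence has a named cell in the accuracy table. Comparing the intent-to-treat and per-protocol sets would show how many patients were set aside. This stands in part. It protects the primary result for pN+ patients, but a pN0 patient without a map is scored as a correct result. The difference between the two analysis sets also mixes failed injections with other treatment deviations.

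A second objection is to the size. The cited rates come from sentinel-node work, which the protocol itself contrasts with mapping of the whole collector. This stands: the counts are illustrative, and both ends of the 80–98% range must be shown.

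Third, a reader might infer that patients without fluorescence are declared feasible, or that the trial would report 100% feasibility when spillage is nil. The documents do not support this. They define a failure proportion, never convert it to its complement and label no patient as feasible. With no spillage the plan would report 0% spillage.

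A reader might also take the design section's remark that "the main focus of the study is investigation of ICG lymphatic mapping feasibility" as raising this endpoint to the centre of the trial. That section describes the feasibility under study as defining margins by comparing dye spread with metastatic spread, which is the primary comparison, not this secondary endpoint.

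Finally, the mapping procedure and fluorescence assessment are set out in Appendix S1, which is not shown. It may say how failed mapping is handled, but it would not alter the endpoint wording in the two places where it is fixed.

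**Conclusion.** The point holds as a defect in how a secondary endpoint is defined. Feasibility as written captures one failure mode out of at least three that the protocol foresees, and so understates how often mapping leaves no usable ICG border. By how much is unknown: about 6 to 9 of 101 patients if the cited sentinel-node detection rates applied, and 2 to 20 over the quoted range, assuming no overlap with spillage.

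The consequence is limited. The endpoint is descriptive, with no test or decision rule attached. This point does not affect the sample size, the primary endpoint or the 96% criterion, and it should not be read as evidence that the sensitivity analysis is invalid.

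**What to change.** In both the Endpoints section and Table 2, define feasibility as the proportion of patients with attempted mapping who have an interpretable ICG border, meaning fluorescence present and no spillage or other technical defect affecting interpretation. Report it with a 95% confidence interval, and list interpretation-affecting spillage, absent fluorescence and other defects as separate components.

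The main components are already recorded: technical defects and presence of fluorescence. What is not described is a judgement on whether a non-spillage defect affected interpretation. For patients already operated on, that would need some review of the stored procedure recordings. The reported figure is likely to be slightly less favourable. No additional patients or procedures are needed.
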